### Randomization

This study employs a single-center, randomized controlled, prospective design to ensure scientific rigor and precision. Eligible patients will be randomly assigned to either the RIC group or the sham RIC group. Randomization will be conducted using opaque envelopes. Sealed, numbered, opaque envelopes containing the group assignments will be opened by a researcher not involved in the study design or data analysis, in the order of participant enrollment. The subjects, researchers, and evaluators will be blinded to the treatment allocation.

### Interventions

All study participants will undergo bilateral limb RIC using the Doctormate IPC-906, manufactured by Beijing Renqiao Neuroscience Institute. Electronic tourniquet cuffs will be placed on both arms of each participant (Figure 1).

**Figure 1 fig1:**
[figure not shown]
Device for remote ischemic conditioning.

Lacking clinical RIC studies in AD populations, there are no intervention data available for direct reference. In a study published in Lancet Neurology, [name] and colleagues demonstrated that a 45 min daily RIC protocol significantly reduced the recurrence of strokes and the incidence of cardiovascular events in individuals with intracranial atherosclerotic stenosis (23). Additionally, AD research on Transcranial Magnetic Stimulation and Transcranial Direct Current Stimulation has shown cognitive improvements with 2 to 6 months of non-pharmacological treatment (24, 25). As an initial to evaluate safety, the duration of RIC in this study has been set at 3 months. In the RIC group, each session will involve five cycles of cuff inflation to 200 mmHg for 5 min, followed by a 5 min deflation period, conducted daily for 45 min. The sham RIC group will follow an identical schedule, with cuff inflation limited to 60 mmHg for 5 min, followed by a 5 min deflation period, repeated five times per session, once daily, for 45 min. The inflation pressure of 60 mmHg was specifically chosen for the sham group based on previous experience and published protocols, as this level of cuff inflation generates sufficient pressure to mimic the sensation of treatment without inducing true limb ischemia or producing significant physiological changes. Participants undergoing sham procedures typically report a credible sensation similar to active treatment, supporting its validity as a placebo. Additionally, this pressure level aligns with previously validated sham protocols used in multiple high-quality clinical trials (e.g., NCT03868007; ChiCTR2000041042), which have demonstrated strong blinding effectiveness and placebo credibility (26, 27).

The RIC intervention requires participants to attend their assigned community health service stations daily during designated time slots for RIC training. At these facilities, they will use specialized RIC equipment to conduct the sessions as outlined in the study protocol. A dedicated team of specialists will be available to provide comprehensive guidance and support throughout the process, ensuring participant safety, promoting treatment adherence, and maintaining the efficacy of the sessions.

To evaluate the long-term efficacy of RIC, the study includes a 12-month follow-up period with assessments at 6 and 12 months. These evaluations include neurocognitive scales and blood biomarkers analyses. The RIC intervention itself is administered over a 3-month period, with data collection points at baseline, 3 months, 6 months, and 12 months to systematically assess its sustained effects (Figure 2).

**Figure 2 fig2:**
[figure not shown]
Timeline for experimental procedures.

### Neuropsychological assessments

The Mini-Mental State Examination (MMSE), Montreal Cognitive Assessment (MOCA), and Clinical Dementia Rating (CDR) scales will be used to evaluate the cognitive function of patients with mild Alzheimer’s dementia. The Activities of Daily Living (ADL) scale will be used to assess their quality of life. The Hamilton Anxiety Rating Scale (HAMA) and the Hamilton Depression Rating Scale (HAMD-17) will be used to evaluate the mental and emotional status. These assessments will be conducted at baseline, 3 months, 6 months, and 12 months.

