**Methods and expected results:**

This study is a randomized, controlled, single-center, prospective clinical trial designed to evaluate the safety, feasibility, and preliminary efficacy of RIC in patients with mild Alzheimer’s dementia. Eligible participants will be recruited and randomly assigned to either the RIC group or a control group receiving sham RIC, with 20 patients in each group. Participants will receive either RIC or sham RIC once daily over a 3-month period. Outcome measures will assess cognitive function, psychological well-being, and inflammatory and neurodegenerative biomarkers. Psychiatric adverse events will be monitored throughout the treatment using the Hamilton Anxiety Rating Scale (HAMA) and the Hamilton Depression Rating Scale (HAMD-17). Cognitive function and daily living abilities will be evaluated at baseline, 3 months, 6 months, and 12 months post-treatment using the Mini-Mental State Examination (MMSE), Montreal Cognitive Assessment (MoCA), Clinical Dementia Rating (CDR), and the Activities of Daily Living (ADL) scales. In addition, blood samples will be collected at each time point to measure plasma biomarkers of *β*-amyloid species and serum inflammatory cytokines to assess potential changes in cognitive decline, disease progression, and inflammation. The primary endpoint is safety, with the expectation that RIC will not increase psychiatric adverse events as reflected in HAMA and HAMD-17 scores. Primary efficacy endpoints include improvements in MMSE, MoCA, CDR, and ADL scores, indicating potential cognitive benefits and enhanced daily functioning. Secondary endpoints will analyze biomarkers to evaluate disease progression and inflammation levels before and after treatment.

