## Outcomes

### Outcomes for safety

The primary safety outcomes of this study are to evaluate the safety profile of RIC. Specifically, the following adverse events will be monitored:

1)  Psychological and Emotional Impact: Clinical observations and previous research have highlighted that patients with AD often experience feelings of helplessness and depression as their cognitive function declines and their ability to perform daily activities diminishes. These emotional challenges can lead to anxiety and fears about disease progression. Additionally, the pressure sensation caused by RIC training may exacerbate these feelings. To address this, the psychological condition of patients will be assessed using the HAMA and the HAMD-17, and the incidence of related adverse events will be calculated.2)  Procedure Tolerability: Instances of participants being unable to tolerate either the RIC or sham RIC procedures, resulting in suspension from the study, will be recorded as adverse events.3)  Physical Injuries: Signs of tissue or neurovascular injury potentially caused by RIC or sham RIC procedures will be monitored. This includes assessments such as palpation of the distal radial artery for pulsation, visual inspection for local edema, erythema, or skin damage, and palpation for tenderness in the affected areas.4)  Vital Sign Monitoring: Participants’ vital signs, including body temperature, respiratory rate, blood pressure, and heart rate, will be recorded to identify any potential systemic effects of the intervention.

All adverse events will be reviewed and independently determined by trained members of the research team who are blinded to the randomization group. These outcomes aim to comprehensively evaluate the safety of RIC and ensure that any risks associated with the intervention are carefully monitored and managed.

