In this study, participant safety is closely monitored through structured safety management protocols. If a participant experiences psychiatric worsening, indicated by significant increases in anxiety or depression scores (HAMA or HAMD-17), an immediate referral to a psychiatrist will be initiated, and psychiatric interventions or modifications to study procedures may be recommended as appropriate. In cases of physical injury, such as tissue damage, neurovascular compromise, or significant pain related to the cuff procedure, the intervention will be immediately paused. A multidisciplinary specialist team, including experts in neurology, cardiology, neurosurgery, and vascular surgery, will promptly evaluate the participant. Treatment will be provided as needed, and the participants will be closely monitored until full resolution. Detailed records of these events will be documented and reviewed by our Data and Safety Monitoring Board (DSMB) to ensure thorough oversight and appropriate follow-up actions.

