### Statistical analysis

Data will be obtained from all patients who complete the study protocols and follow-ups and will be analyzed using the per-protocol (PP) approach. Statistical analysis will be performed using SPSS version 20 (SPSS Inc., Chicago, IL, United States), with a significance level of *p* < 0.05. Demographics and clinical characteristics will be analyzed using descriptive statistics. Continuous and categorical data will be reported as mean values, standard deviations, number values, and percentages. Continuous variables following a normal distribution will be compared using the independent samples *t*-test, ANOVA, or rank-sum test, while categorical variables will be compared using the chi-square test.

In our RIC trial in mild Alzheimer’s dementia (*n* = 40), we implemented two strategies appropriate for small-sample longitudinal data. First, single random forest imputation was applied to address missing cognitive scores (e.g., MoCA/MMSE) by using predictors such as baseline Aβ42/Aβ40 ratio and RIC adherence preserve variable interaction structure. Second, Generalized Estimating Equations (GEE) will be used to model outcome trajectories under the assumption of missing at random (MAR), thereby accommodating incomplete data without imputation. Attrition is minimal (7% MoCA loss at 12 months) and APOE subgroup analyses show no evidence of differential dropout. This approach balances methodological rigor with feasibility and aligns with CONSORT recommendations for early-phase trials with limited resources.

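### No HAMA or HAMD-17 rating is scheduled within the 3 months of daily sessions or at early stopping, although the abstract promises monitoring throughout treatment, and the completers-only analysis drops those who stop

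*Protocol article*

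**What the plan says.** All references are to the protocol article.

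- **Abstract, methods and expected results.** The monitoring is described as continuous: "Psychiatric adverse events will be monitored throughout the treatment using the Hamilton Anxiety Rating Scale (HAMA") and the HAMD-17. The next sentence gives the cognitive and daily-living scales their own fixed visits. Safety is the primary endpoint, and the expectation is that "RIC will not increase psychiatric adverse events as reflected in HAMA and HAMD-17 scores".
- **Neuropsychological assessments.** After naming the cognitive scales, the ADL, the HAMA and the HAMD-17, the section closes with one schedule for all of them: "These assessments will be conducted at baseline, 3 months, 6 months, and 12 months".
- **Study design.** Treatment is once daily for 3 months.
- **Outcomes for safety.** A reason for harm during sessions is given: "the pressure sensation caused by RIC training may exacerbate these feelings". The two scales are the stated response, and "the incidence of related adverse events will be calculated". Inability to tolerate the procedure that leads to suspension is itself an adverse event. Psychiatric worsening, "indicated by significant increases in anxiety or depression scores (HAMA or HAMD-17"), leads to immediate psychiatric referral and possibly to changes in study procedures.
- **Statistical analysis.** "Data will be obtained from all patients who complete the study protocols and follow-ups", with a per-protocol approach. No separate population is named for safety.

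**The concern.** The abstract promises on-treatment monitoring by two named scales, and the methods give those scales a schedule with no on-treatment visit. The exposure the protocol worries about, cuff pressure, starts at the first session and ends at month 3. The scheduled ratings fall before it, at its end, and after it.

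Three things are at stake. The score-based part of the primary safety expectation cannot reflect worsening that comes and goes within the 3 months. The referral and modification rule has no planned score to act on until sessions are over, when treatment can no longer be modified. And a participant who stops early because of distress has no rating tied to stopping and, on the literal wording of the analysis section, is not analysed.

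**Working it through.** The plan states no figure here to reproduce. The check is a count of visits and a comparison of sections.

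**1. Sessions.** One a day for 3 months: 3 × 28 = 84 days at the short end, up to 92 calendar days at the long end, so about 90.

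**2. Scheduled ratings during treatment.** Rating months are {0, 3, 6, 12}; treatment occupies months 0 to 3. Ratings strictly between 0 and 3: **0**. The longest stretch of treatment without a scheduled rating is therefore the whole of it, about 13 weeks. The ratings at 6 and 12 months fall after treatment ends.

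**3. Does another section supply a rating?** The follow-up text under Interventions repeats the same four time points but names neurocognitive scales and biomarkers, not these two scales, so it neither adds a visit nor confirms the schedule for them. Outcomes for safety uses the scores but gives no rating date. Figure 2, the timeline, is not shown.

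**4. The referral and modification rule.** Its score input is a rise in HAMA or HAMD-17. By step 2, the first planned post-baseline score is at month 3, when sessions end. Before that, the rule can act on a score only if someone decides to take an unscheduled one.

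**5. The analysis population.** Take the tolerability outcome, and assume that a suspended participant does not go on to complete the protocol. Let k of the 20 participants in a group be suspended for intolerance.

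- Incidence among all treated: k/20.
- Incidence among completers: 0/(20 − k) = 0, whatever k is.

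Each such participant is 1/20 = 5 percentage points of the group's incidence, and the completers-only analysis shows none of it. The same exclusion would remove any HAMA or HAMD-17 rating taken when a participant stops. Adding ratings without changing the population would therefore not be enough.

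**6. Size of the addition.** One on-treatment rating for each participant is 40 × 1 = 40 ratings; two is 40 × 2 = 80. If 5% to 20% stop early (an assumption), that adds 2 to 8 ratings. At an assumed 20 to 40 minutes for both scales, the total runs from 42 × 20/60 = 14.0 to 88 × 40/60 = 58.7 rater-hours, before travel.

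**The case against.** The strongest case on the other side has four parts.

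*Figure 2 may show on-treatment ratings, and the text never says the scales are given only at four visits.* This stands as a condition. Fixed visits plus ratings on clinical concern is a coherent reading, and nothing bars unscheduled ratings. But the only schedule in the text for these scales has no on-treatment visit, which does not match the abstract.

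*Other safeguards cover the period.* This largely stands. The protocol requires "participants to attend their assigned community health service stations daily during designated time slots", with a specialist team available; intolerance leading to suspension is recorded; adverse events are judged by blinded staff; and the monitoring board reviews safety data. A reader might infer that psychiatric safety goes unmonitored during treatment. The document does not support that: overt distress can be noticed and recorded. What these safeguards do not supply is the scale scores on which the abstract and the referral rule rely.

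*The share of episodes missed is unknown.* This stands. Any detection percentage depends on assumed onset and duration, for which the document gives no basis, so none is offered here. For the same reason the document does not single out particular weeks as the right ones.

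*The analysis population is a separate matter, and the planned generalized estimating equations accommodate incomplete data.* The first half is fair as classification, but the two gaps act on the same participants. The second half does not answer the point: the sentence concerns modelling of outcome trajectories and does not restore to the safety analysis people whom the opening sentence of that section leaves out. It does make the section internally mixed, which is why the conclusion is put as the literal reading.

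An article may also leave early-stop visits to the full protocol. The firm points are what this text fixes: a four-visit schedule, a promise of monitoring throughout treatment, and a completers-only analysis.

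**Conclusion.** The point holds and should be fixed. Subject to Figure 2, no HAMA or HAMD-17 rating is scheduled within about 90 daily sessions, none is tied to early stopping, and the wording of the analysis section removes non-completers from the primary safety analysis.

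The harm is bounded. It concerns worsening that resolves before month 3, or that is present when a participant stops, and that staff do not otherwise notice. Worsening that persists to month 3 is already rated in participants still in follow-up. The analysis-population part is the firmest: it needs no assumption about onset or duration, only that a participant suspended for intolerance does not complete. The count of zero on-treatment ratings needs no assumption beyond the unseen figure.

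**What to change.** 1. **Statistical analysis.** State that all safety outcomes, including HAMA, HAMD-17 and intolerance events, are analysed in everyone who received at least one session. This needs no data beyond what is already to be collected, and it ensures that early-stop ratings count.
2. **Neuropsychological assessments.** Add at least one or two on-treatment HAMA and HAMD-17 ratings by the existing blinded evaluators. Place the first in the early weeks, because cuff pressure acts from the first session; the exact weeks are for the investigator to choose. Add a rating when a participant stops sessions. Keep unscheduled ratings on clinical concern.
3. **Outcomes for safety.** Use these ratings for the incidence of psychiatric adverse events and as scheduled input to the referral and modification rule. The abstract is then correct as it stands.

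If Figure 2 already shows on-treatment ratings, the assessment text need only be aligned with it; the analysis population and any missing early-stop rating would still need attention.

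The cost is a protocol amendment, 40 to 80 extra ratings plus one per early stopper, and added interview burden for people with mild dementia. Sessions take place at community stations and the document does not place blinded raters there, so scheduling or travel is a real further cost that is not counted in the hours above.

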### Blood sample collection and analysis

Under fasting conditions, 5 mL of peripheral venous blood will be drawn, and the plasma samples will be stored in a − 80°C freezer. Enzyme-linked immunosorbent assay (ELISA) will be used to measure serum levels of interleukin-1β (IL-1β), interleukin-6 (IL-6), interleukin-8 (IL-8), interleukin-10 (IL-10), interleukin-2 receptor (IL-2R), tumor necrosis factor-*α* (TNF-α), erythrocyte sedimentation rate (ESR), C-reactive protein (CRP), and plasma biomarkers including glial fibrillary acidic protein (GFAP), phosphorylated tau at positions 181, 217, and 231 (pTau181, pTau217, and pTau231), Aβ42 and Aβ40 and their ratios, and neurofilament light chain (NfL). These measurements will be conducted at baseline, 3 months, 6 months and 12 months.

## Outcomes

### Outcomes for safety

The primary safety outcomes of this study are to evaluate the safety profile of RIC. Specifically, the following adverse events will be monitored:

1)  Psychological and Emotional Impact: Clinical observations and previous research have highlighted that patients with AD often experience feelings of helplessness and depression as their cognitive function declines and their ability to perform daily activities diminishes. These emotional challenges can lead to anxiety and fears about disease progression. Additionally, the pressure sensation caused by RIC training may exacerbate these feelings. To address this, the psychological condition of patients will be assessed using the HAMA and the HAMD-17, and the incidence of related adverse events will be calculated.2)  Procedure Tolerability: Instances of participants being unable to tolerate either the RIC or sham RIC procedures, resulting in suspension from the study, will be recorded as adverse events.3)  Physical Injuries: Signs of tissue or neurovascular injury potentially caused by RIC or sham RIC procedures will be monitored. This includes assessments such as palpation of the distal radial artery for pulsation, visual inspection for local edema, erythema, or skin damage, and palpation for tenderness in the affected areas.4)  Vital Sign Monitoring: Participants’ vital signs, including body temperature, respiratory rate, blood pressure, and heart rate, will be recorded to identify any potential systemic effects of the intervention.

All adverse events will be reviewed and independently determined by trained members of the research team who are blinded to the randomization group. These outcomes aim to comprehensively evaluate the safety of RIC and ensure that any risks associated with the intervention are carefully monitored and managed.

In this study, participant safety is closely monitored through structured safety management protocols. If a participant experiences psychiatric worsening, indicated by significant increases in anxiety or depression scores (HAMA or HAMD-17), an immediate referral to a psychiatrist will be initiated, and psychiatric interventions or modifications to study procedures may be recommended as appropriate. In cases of physical injury, such as tissue damage, neurovascular compromise, or significant pain related to the cuff procedure, the intervention will be immediately paused. A multidisciplinary specialist team, including experts in neurology, cardiology, neurosurgery, and vascular surgery, will promptly evaluate the participant. Treatment will be provided as needed, and the participants will be closely monitored until full resolution. Detailed records of these events will be documented and reviewed by our Data and Safety Monitoring Board (DSMB) to ensure thorough oversight and appropriate follow-up actions.

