### Sample size estimation

This is a Phase I trial measuring the safety and feasibility of RIC. Since no prior clinical studies have examined RIC in AD patients, there is no reference data available. Ganesh proposed that a cohort of 12 patients per group is sufficient to assess the safety of remote ischemic conditioning in patients with Vascular Cognitive Impairment (28). Tong’s Phase I clinical trial on the safety and efficacy of RIC in stroke patients suggested that 20 cases are sufficient to assess the feasibility of a pilot study (29). Based on studies addressing the safety and feasibility of RIC, this project targets 20 patients in each group, providing sufficient confidence to proceed to a subsequent Phase II study with a randomized sham control.

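### The primary psychiatric safety outcome is reported only as an event incidence among completers; the HAMA and HAMD-17 scores already collected should be compared beside it

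*Protocol article*

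**What the plan says.** The abstract (Methods and expected results) sets the aim: "The primary endpoint is safety, with the expectation that RIC will not increase psychiatric adverse events as reflected in HAMA and HAMD-17 scores".

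Outcomes for safety gives that aim its form. Psychological condition is assessed with the two scales, and "the incidence of related adverse events will be calculated". Adverse events are determined by team members blinded to allocation. The closing paragraph on safety management describes worsening that leads to psychiatric referral as "indicated by significant increases in anxiety or depression scores".

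Neuropsychological assessments says of all the scales, HAMA and HAMD-17 included: "These assessments will be conducted at baseline, 3 months, 6 months, and 12 months". Outcomes for efficacy lists the secondary outcomes, and the two Hamilton scales are not among them.

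On size, "this project targets 20 patients in each group", set by precedent from earlier RIC studies. Statistical analysis takes a per-protocol approach, using participants who complete the protocol and follow-up. It gives generic tests: chi-square for categorical variables, t-test, ANOVA or rank-sum for continuous ones. It does not name HAMA or HAMD-17.

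**The concern.** The result the trial hopes for is an absence of harm, so an insensitive analysis favours the hoped-for answer. The plan itself says that cuff pressure may make anxious or depressed feelings worse, so harm is plausible. Yet as the outcome is written, two numeric scales measured four times per participant enter the primary safety result only as a yes/no count.

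The completer restriction adds to this. Participants who give up daily sessions because of distress are the ones a psychiatric safety analysis most needs, and a per-protocol set can leave them out.

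At stake is the decision to proceed to Phase II, which the plan says this sample will support. A non-significant difference in event counts could be read as reassurance when the comparison had little chance of showing a real shift.

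**Working it through.** **Plan's own figure.** The 20 per group comes from precedent. No effect size, event rate, margin or power is given, so there is nothing to reproduce or contradict.

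**Inputs from the plan.** n = 20 per arm; significance level 0.05 (sidedness not stated, two-sided assumed).

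**Assumptions, because the plan gives no reference data.** Normal scores; RIC raises every participant's score by d = 0.5 or 0.8 SD; control incidence p0 = 5%, 10% or 20%; baseline to follow-up correlation r = 0.6; all 20 per arm evaluable.

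**Effective shift for each analysis.**
- Follow-up score: d.
- Change from baseline: d/√(2(1 − r)) = d/√0.8, so 0.8 becomes 0.894 and 0.5 becomes 0.559.
- Baseline-adjusted score: d/√(1 − r²) = d/0.8, so 0.8 becomes 1.0 and 0.5 becomes 0.625.

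**Event rate in the RIC arm.** A cut that gives control incidence p0 gives p1 = 1 − Φ(z₁₋ₚ₀ − shift). At d = 0.8, cutting the follow-up score takes 5% to 19.9%, 10% to 31.5% and 20% to 48.3%. Cutting change takes them to 22.6%, 34.9% and 52.1%.

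**Power.** Chi-square by exact binomial enumeration (uncorrected); scores by the noncentral t.

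| Analysis, 20 per arm | d = 0.5 | d = 0.8 |
|---|---|---|
| Incidence cut from follow-up score (p0 = 5/10/20%) | 10/17/22% | 29/40/49% |
| Incidence cut from change (p0 = 5/10/20%) | 13/20/27% | 37/49/58% |
| t-test on follow-up score | 34% | 69% |
| t-test on change | 41% | 79% |
| Baseline-adjusted score | 49% | 87% |

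Like for like, a cut of change (37% to 58%) compares with 79% for the change score itself, and a cut of the follow-up score (29% to 49%) with 69%.

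**Sensitivity under a uniform shift.** For the follow-up cut at 0.8 SD, control rates of 30% or 50% still give only 48% to 49%, and Fisher's test gives 17% to 37% across control rates of 5% to 50%. Adjusted-score power at 0.8 SD is 73% with r = 0.3 and 81% with r = 0.5.

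**When harm is confined to a subset.** Suppose each RIC participant has a 25% chance of worsening by 3 SD and the rest are unaffected (illustrative). Then p1 = 0.75·p0 + 0.25·[1 − Φ(z₁₋ₚ₀ − 3)]. Incidence power is 53%, 49% and 40% at control rates of 2%, 5% and 10%, against about 38% (by simulation) for an unadjusted t-test. At a 20% control rate it is 28%, below the t-test. The ranking therefore reverses when the control rate is low.

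**Precision of the proposed estimate.** The 95% half-width for the adjusted difference is about 2.03 × √(2/20) × 0.8 = 0.51 SD.

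**The case against.** Much of the case on the other side stands.

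- *A reader might infer that any cut-off wastes information.* That is true for a shift across the arm. It fails when a few participants worsen a lot, which is a natural pattern for adverse events. Replacing the incidence with a mean difference would be a trade-off, so the incidence should stay.
- *A reader might infer that the cut will be chosen after scores are seen.* Nothing in the article says so. Event assessors are blinded, and immediate referral during the trial implies that some working rule operates before the data are complete.
- *A reader might treat the missing threshold as an error in itself.* An event definition can sit in the full protocol or analysis plan, which are not shown. The phrase "indicated by significant increases in anxiety or depression scores" describes a referral trigger and need not be the endpoint definition. That events are cut from the scores at all is a reading of several places together; they may be judged clinically.
- *Score comparisons are not ruled out.* The abstract ties the endpoint to the scores, and the generic t-test, rank-sum and GEE provisions could cover them. The loss therefore applies to the outcome as written and not to every analysis the data allow. Chi-square for the incidence is likewise inferred from the generic line.
- *This is Phase I.* No power for harm is claimed, and reporting event incidence is ordinary practice. The point asks for no more participants, only fuller use of scores already collected.
- *Participants who cannot tolerate the procedure are recorded as adverse events.* This captures some of them, but the completer restriction leaves it unclear whether they enter the comparison.

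**Conclusion.** The point holds in a limited form. The article states the primary psychiatric safety outcome only as an incidence, names neither Hamilton score as an outcome, and restricts analysis to completers. Under a shift across the arm, the incidence is clearly the weaker comparison: 37% to 58% or 29% to 49% power at 0.8 SD, against 87% for baseline-adjusted scores; 13% to 27% or 10% to 22% at 0.5 SD, against 49%.

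These sizes rest on assumed normal scores, a uniform shift, r = 0.6, control incidence of 5% to 20% and no dropout. Part of the gap to 87% comes from using the baseline efficiently and not from avoiding the cut. The documents do not support going further: the incidence is not the wrong measure in general, no stated figure is contradicted, and there is no sign of a cut chosen to suit the data. Each summary sees a kind of harm that the other can miss, so the plan should report both.

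**What to change.** - Keep the event incidence. Beside it, prespecify the baseline-adjusted difference between arms at 3 months in HAMA and in HAMD-17, each with a 95% confidence interval.
- Run this in all randomised participants with available scores, including those who stopped sessions early, and not only in completers.
- Base any statement that RIC does not increase anxiety or depression on the upper confidence limits, not on p > 0.05. With a half-width near 0.51 SD under the assumptions above, such a statement will be modest, and the report should say so.
- The clinical team should fix the definition of a psychiatric event before unblinding and reconcile the incidence wording with the referral wording, both in Outcomes for safety. No value is proposed here.

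The cost is some wording and one extra model, applied to each scale. No new data or participants are needed. The downside is two co-reported psychiatric safety summaries, which may differ; the plan should say in advance that both are shown whatever they find.
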